## Abstract

**Background:**

Knee osteoarthritis (KOA) is reputedly the most common musculoskeletal disease of the lower limbs and the main cause of pain and disability among older individuals. Pain is the most significant and widespread symptom of KOA. The descending pain inhibitory system has a cardinal role in normal pain consciousness, and its malfunction may be one of the pathophysiological mechanisms in KOA. Crucially, the rostral ventromedial medulla (RVM) and periaqueductal gray (PAG), as important components of the descending pain inhibitory system, directly modulate the activity of the spinal neurons involved in pain transmission. Tuina, a manual therapy, is effective and safe for reducing clinical symptoms of KOA; however, the mechanism that influences pain through the descending pain inhibitory system in KOA is unclear.

**Objective:**

This study aims to investigate the modulatory implications of Tuina on the RVM and PAG, which have critical roles in the descending pain inhibitory system in patients with KOA.

**Methods:**

This randomized controlled parallel trial will be conducted at the Tuina Clinic of the Third Affiliated Hospital of Henan University of Chinese Medicine (Zhengzhou, China). Patients with KOA will be randomly assigned (1:1) to 6 weeks of health education or Tuina. All patients in both groups will accept a resting-state functional magnetic resonance scan at the beginning and end of the experiment, and the resting-state functional connectivity and the voxel-based morphometry analysis will be performed to detect the RVM and PAG function and structure changes. The clinical outcome assessments will be (1) the pressure pain thresholds, (2) the Numerical Rating Scale, (3) the Hamilton Depression Scale (HAMD), and (4) the Western Ontario and McMaster Universities Osteoarthritis Index (WOMAC). Considering that this trial is a study of resting-state functional magnetic resonance imaging technology, resting-state functional connectivity and voxel-based morphometry are the primary outcomes, and clinical outcome assessments are secondary outcomes. Adverse events will be documented and assessed throughout. All main analyses will be carried out on the basis of the intention-to-treat principle. The outcome evaluators and data statisticians will be masked to the treatment group assignment to reduce the risk of bias.

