### Sample Size

The sample size of 64 patients was planned, based on our previous clinical research [9]. The formula is determined:

wherein *N* refers to the sample size in each group, *σ* represents the SD, *α* represents type I error, *β* represents type II error, 1–*β* represents the test power, and *δ* represents the difference between mean groups.

The pressure pain threshold (PPT) values of the treatment and control groups were 9.53 (1.26) and 9.02 (2.62), respectively. We took *α*=0.05, *β*=0.10, 1–*β*=0.90, set the 2-sided test level *α*=0.05, and found out from the *t*-distribution boundary value table: *u*_α_=1.96, *u*_β_=1.282. In this study, *δ*=0.51, *σ* with the larger SD of 1.36, and an approximate *N* of 29 after substituting the formula. With an estimated drop-off rate of 10%, a total of 64 patients with KOA were needed.

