### Randomization

Independent research staff will use SPSS 25.0 (IBM Corp) to generate a randomly numbered sequence for complete randomization. Participants will be randomly assigned into 1 of 2 groups (ie, health education or Tuina group) and applied in a 1:1 allocation ratio. The random sequence will be sealed by a self-governing research assistant via an opaque envelope that contains information regarding the participant’s allocation.

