### Clinical Outcome Assessments

Validated pain detectors and questionnaires will be used to assess knee pain, psychological characteristics, and function at the beginning and end of the experiment. The clinical outcome assessments will be (1) the PPTs, (2) the NRS, (3) the Hamilton Depression Scale (HAMD), and (4) the Western Ontario and McMaster Universities Osteoarthritis Index (WOMAC). Additional outcome indices included the adverse events of treatment.

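### The only sample size and power calculation is on PPT, a secondary outcome; no power justification is given for the primary outcomes rsFC and VBM, and the stated 90% does not hold for PPT either

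*Protocol article*

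**What the plan says.** **Outcome hierarchy.** The Abstract (Methods) states that "resting-state functional connectivity and voxel-based morphometry are the primary outcomes, and clinical outcome assessments are secondary outcomes". The Clinical Outcome Assessments section puts PPT at the head of the clinical list: "The clinical outcome assessments will be (1) the PPTs, (2) the NRS". PPT is therefore a secondary outcome.

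**Sample size.** The Sample Size section bases the trial on the investigators' earlier clinical study and on one variable: "The pressure pain threshold (PPT) values of the treatment and control groups were 9.53 (1.26) and 9.02 (2.62), respectively". It then says "set the 2-sided test level *α*=0.05", with power 0.90, δ = 0.51, and σ = 1.36, described as the larger of the SDs. The result is about 29 per group. It concludes: "With an estimated drop-off rate of 10%, a total of 64 patients with KOA were needed". Randomization is "applied in a 1:1 allocation ratio".

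**How the primary outcomes are tested.** Under rsFC Preprocessing, left and right PAG and RVM seeds are each correlated with every voxel of the brain. Under rsFC Analysis, ROI-to-ROI connections are judged at an FDR-corrected 5% level, and maps at a voxel-wise .005 threshold with Monte Carlo correction to 5%. Under VBM Analysis, group differences are judged at 5% with family-wise error correction. These sections give thresholds only. Nowhere does the protocol give an expected effect, an SD or a power figure for rsFC or VBM.

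**The concern.** A sample size calculation supports the outcome it is made for, at the error rate it assumes. Here that is one two-sided 5% test of a PPT mean difference. The declared primary analyses concern other variables under other error control, so even a correct PPT calculation would say nothing about them.

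The stated objective is modulation of the RVM and PAG. If the imaging comparison is not significant, its interpretation depends on what the trial could have detected. A paper that reports a formal 90% power calculation, without saying that it does not cover the primary outcomes, makes it easier to take such a result as evidence that Tuina does not act on this system. The Limitations and Strengths section does not mention the issue.

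**Working it through.** **1. The plan's own figure.** The displayed formula could not be read in the text available for this check, so the standard forms were tried. Inputs, all from Sample Size: δ = 0.51, σ = 1.36, u_α = 1.96, u_β = 1.282.

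For two independent groups, n per group = 2σ²(u_α + u_β)²/δ².

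(1.96 + 1.282)² = 10.511, so n = 2 × 1.8496 × 10.511 / 0.2601 = 149.5, or 150 per group.

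This does not reproduce 29, and neither do the variants:

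| Variant | n per group |
|---|---|
| σ = 1.36, as stated | 150 |
| σ = 1.36, one-sided 5% | 122 |
| σ = 1.36, 80% power | 112 |
| σ = 1.36, factor 2 omitted | 75 |
| σ = 1.36, that result halved | 37 |
| σ = 1.26 (smaller listed SD) | 129 |
| σ = 2.06 (pooled from 1.26 and 2.62) | 342 |
| σ = 2.62 (larger listed SD) | 555 |

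The value 1.36 matches neither listed SD (1.26 and 2.62). Solving for the SD that gives 29: σ = 0.51 × √(29/2)/3.242 = 0.60, or 0.85 if the factor 2 is omitted.

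The dropout step is consistent: 58 × 1.1 = 63.8 and 58/0.9 = 64.4, against the stated 64.

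**2. Power for PPT at 29 per group** (two-sided 5%, noncentral t, 56 df): 0.33 with σ = 1.26, 0.29 with σ = 1.36, 0.11 with σ = 2.62. The normal approximation gives 0.34, 0.30 and 0.11.

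**3. What 29 per group can detect on any single outcome.** No required n can be computed for rsFC or VBM, because no effect size or SD is given. A standardized benchmark can be: d = (u_α + u_β)√(2/n).

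- 90% power: 3.242 × √(2/29) = 0.85; noncentral t gives 0.87.
- 80% power: 2.802 × √(2/29) = 0.74; noncentral t gives 0.75.

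For assumed effects (not from the documents; normal approximation, one test at two-sided 5%):

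| Assumed d | Power at 29 per group | n per group for 90% power |
|---|---|---|
| 0.3 | 0.21 | 234 |
| 0.5 | 0.48 | 85 |
| 0.8 | 0.86 | 33 |

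**4. Baseline adjustment.** An adjusted analysis multiplies the detectable difference by √(1 − r²), where r is the correlation between baseline and follow-up. The protocol gives no r. For assumed r of 0.3, 0.5 and 0.7, the 90% figure is 0.866 × 0.954 = 0.83, 0.866 × 0.866 = 0.75 and 0.866 × 0.714 = 0.62.

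**The case against.** **The calculation is open about what it covers.** Sample Size names PPT and nowhere attaches 90% to imaging. That stands: a reader might infer that the protocol claims 90% power for its primary question, but it does not say so. The fault is that the only justification offered for 64 patients belongs to a secondary outcome, without comment.

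**Imaging power is unknown, not shown to be low.** This also stands. A reader might infer that the primary outcomes have little or no power. The documents do not support that, because power depends on an effect size and variance they do not give. A large enough imaging effect would be detectable with 29 per group.

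**Harsher benchmarks do not fit the plan.** It is tempting to split 5% over the four seeds, or to put the voxel-wise .005 into a power formula. The plan uses FDR, Monte Carlo cluster correction and family-wise error control, not a Bonferroni split over seeds. The .005 is a threshold applied before cluster correction, not the level of a test. Neither describes the planned analysis, so only the single-test 5% figure is used here, as a best case.

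**A mechanistic imaging trial may be sized on feasibility, and the article is condensed.** Feasibility would be an acceptable basis, but it is not the one given. A fuller document might add an imaging rationale. That carries little weight, because the article does set out inputs, method and result, and presents PPT as the reason for 64.

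**Conclusion.** The point holds in this form: the protocol gives no power justification for rsFC or VBM, its sole calculation is on a secondary outcome, and its 90% figure does not apply to the primary question. On that section's own inputs the figure is not reached for PPT either: about 150 per group would be needed with SD 1.36 and about 555 with SD 2.62, and power at 29 per group is about 0.29 and 0.11 respectively. The PPT error is a separate defect, and correcting it would still leave the primary outcomes without a basis.

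At 29 evaluable per group, the best case is a detectable standardized difference of about 0.87 with 90% power (0.75 with 80%). This assumes one prespecified outcome, normality, equal variances, no baseline adjustment and a two-sided 5% test. The planned corrected analyses will generally need larger effects; how much larger cannot be derived from the document.

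This should be changed. It does not invalidate the trial, but it limits what a null imaging result can support.

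**What to change.** In Sample Size, withdraw the 90% power claim and replace it with text such as:

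> The sample of 64 is not derived from the primary outcomes (rsFC and VBM), for which no effect size was available. With 29 evaluable participants per group, a single unadjusted two-group comparison at a two-sided 5% level detects a standardized difference of about 0.87 with 90% power, or 0.75 with 80% power. The planned multiplicity-corrected whole-brain, ROI and VBM analyses will generally need larger effects, and no power is claimed for them.

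The clause about no available effect size is for the sponsor to confirm or amend. If a smaller, baseline-adjusted figure is quoted, state the assumed correlation beside it. Reconcile the SD of 1.36 with the listed 1.26 and 2.62, or drop the PPT calculation.

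In the analysis and reporting text, commit to giving imaging group differences with 95% CIs and to not reading a non-significant imaging result as absence of modulation.

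The cost is wording and a less favourable stated figure. No extra patients are needed, and it can be done although enrollment has begun. Naming one connectivity endpoint as the sole primary, or adding a baseline-adjusted model, would be a substantive amendment and is not needed for this fix.

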**Results:**

This trial was approved by the ethics committee of the Third Affiliated Hospital of Henan University of Chinese Medicine. Enrollment began in December 2023, and the results of this trial are expected to be submitted for publication in May 2025.

**Conclusions:**

This trial will identify a possible relationship between function and structure changes of RVM and PAG and the improvement of clinical variables, elucidating the effect of Tuina on the descending pain inhibitory system of patients with KOA. This trial will provide much-needed knowledge for Tuina for patients with KOA.

**Trial Registration:**

Chinese Clinical Trial Registry ChiCTR2300070289; https://www.chictr.org.cn/showproj.html?proj=182570

**International Registered Report Identifier (IRRID):**

PRR1-10.2196/52820

## Introduction

Knee osteoarthritis (KOA) is reputedly the most common musculoskeletal disease of the lower limbs and the main cause of pain and disability among older individuals. Approximately 80% of individuals aged 65 years or older show radiological symptoms of KOA [1]. Pain is the most significant and widespread symptom of KOA. International recommendations for KOA treatment consist of pain alleviation and physical interventions via a combination of pharmacological and nonpharmacological therapies, such as massages [2,3]. Tuina, a massage remedy built on Chinese Medicine meridian theories and Zang-Fu organs, consolidates contemporary scientific knowledge, including anatomy, biomechanical role, and physiology. Previous randomized controlled trials (RCTs) have supported the effectiveness of Tuina for the treatment of different health conditions, such as acute bronchitis [4] and musculoskeletal disorders [5,6]. In relation to KOA, 2 systematic reviews have identified positive clinical effects of Tuina in improving the outcomes of patients with KOA [7,8]. Furthermore, our recent RCT demonstrated the safety and effectiveness of Tuina for improving pain, increasing joint flexibility, and improving KOA-related disability [9].

The pathogenesis of KOA is complex and involves heterogeneous factors in the central and peripheral nervous systems. However, peripheral candidate mechanisms are insufficient to explain widespread pain and the range of concomitant symptoms; thus, centrally driven mechanisms are deemed pivotal in the etiology of KOA. Our recent research demonstrated that the brain also participates in the pathophysiological changes in KOA and that central nervous system remodeling and function modifications may be among the central mechanisms associated with KOA [10]. Patients who reported higher levels of arthritic pain had greater opioid receptor availability in the periaqueductal gray (PAG), a key region of the descending pain inhibitory system, suggesting the alteration of this system in KOA [11]. Additionally, a functional magnetic resonance imaging (fMRI) trial demonstrated that the degree of PAG activation provides a sensitive and objective assessment of patellofemoral pain pressure in patients with KOA [12]. The descending pain inhibitory system originates in the PAG of the midbrain conduction duct and exerts its analgesic function through the relay of the rostral ventromedial medulla (RVM), inferior projection neuron of the cephalic medulla, and spinal-thalamic projection neurons in the superficial dorsal horn of the spinal cord [13]. Moreover, the subcortical structures and multiple cortices of the brain, comprising the anterior cingulate cortex, amygdala, insula, and hypothalamus, are also involved in pain modulation via the descending pain inhibitory system. The function of the descending pain inhibitory system in pain modulation and the management of the same have been substantially referenced [14,15].

We have, therefore, designed a single-center, parallel RCT to investigate the implications of Tuina and health education on KOA pain, resting-state functional connectivity (rsFC) of the cardinal regions of the descending pain inhibitory system (RVM and PAG), modifications of the voxel-based morphometry (VBM) of RVM and PAG, and behavioral alterations and their connections. We hypothesized that all treatments would relieve knee pain and share common pathways and that pain relief would be associated with the descending pain inhibitory system.

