### Interventions

A panel of 2 clinical medical professionals with an academic background in Tuina and clinical medicine agreed to develop a standard protocol for Tuina and health education. The protocol’s feasibility will be examined to determine whether it is practicable and acceptable and to identify any realistic issues caused by the procedures. Given the nature of the treatment, participants will be informed that the trial will be without harm, compensation, and posttrial care.

Clinical medical professionals with ≥3 years of experience with Tuina will conduct the health education for the participants. Before the trial, clinicians will be trained to ensure standard procedures and compliance with treatment protocol. All participants in the Tuina group will receive three 20-minute sessions a week over a 6-week treatment course. The participants in the health education group will participate in health education sessions lasting 1 hour each (administered once weekly for 6 weeks). The participants are to maintain their dietary habits and regular physical activity throughout the study period. Throughout the trial, they will be informed that they are not permitted to entertain other remedies. To guarantee compliance, all participants are required to register for therapy in a written log.

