### Health Education

We will introduce the basic concepts of KOA and the methods used to manage the associated risks to help participants protect their knees.

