### VBM Analysis

After completing these image analyses, we will obtain the GMV values of the key regions derived from rsFC for subsequent statistical analysis. The statistical significance between-group differences will be set at *P*<.05 with family-wise error correction.

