### Conclusions

This trial is designed to investigate the central mechanism of Tuina in the treatment of KOA, with the involvement of health education as a control intervention. We expect that Tuina would relieve pain symptoms in patients with KOA and that pain relief would be associated with the descending pain inhibitory system.

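### The hypothesis that both treatments relieve pain through shared pathways is not what the described between-group analysis tests, and the planned within-arm tests cannot establish it

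*Protocol article*

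**What the plan says.** The hypothesis at the end of the protocol's Introduction has three parts. Two are in "We hypothesized that all treatments would relieve knee pain and share common pathways": every treatment relieves pain, and the treatments share pathways. The third is that "pain relief would be associated with the descending pain inhibitory system".

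Other sections set up a comparison:

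- **Abstract, Methods:** "resting-state functional connectivity and voxel-based morphometry are the primary outcomes, and clinical outcome assessments are secondary outcomes".
- **Sample Size:** the calculation is for a difference between two group means in PPT, two-sided at 0.05, and it calls the arms treatment and control.
- **VBM Analysis:** "The statistical significance between-group differences will be set at" the 5% level with family-wise error correction.
- **rsFC Analysis:** correction thresholds are given, but the text does not say whether the contrast is between arms or within an arm.
- **Ranked Data and Count Data:** Mann-Whitney tests between groups and Wilcoxon tests within groups. NRS and WOMAC are among the ranked variables.
- **Conclusions (end of the Discussion):** the trial proceeds "with the involvement of health education as a control intervention", and "We expect that Tuina would relieve pain symptoms in patients with KOA".

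There are two arms, Tuina and health education. Both are scanned and assessed at the beginning and at the end. Eligibility requires a knee pain NRS of 3 or more.

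**The concern.** The Introduction gives health education the same standing as Tuina: a treatment expected to relieve pain by a common mechanism. The sample size, the VBM test and the Conclusions use it as the reference against which an effect of Tuina is sought. The hypothesis and the test therefore answer different questions.

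What is at stake is interpretation. Improvement in both arms is what the Introduction predicts, and it can also occur with no treatment effect. Without a rule set in advance, a null between-group result together with two significant within-arm tests could be reported as confirming that both treatments work through the descending pain inhibitory system.

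**Working it through.** **1. What the sample size is for.** Inputs from Sample Size: δ = 0.51, σ = 1.36, critical values 1.96 and 1.282. The usual formula for comparing two means is n per group = 2[σ(1.96 + 1.282)/δ]².

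- With the stated inputs: 2 × (1.36 × 3.242/0.51)² = 149.5, so 150 per group.
- The protocol states about 29. That figure would need an SD of about 0.51 × √(29/2)/3.242 = 0.60.

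The discrepancy is a separate matter. Two things count here. The calculation targets a difference, and it concerns PPT, which is a secondary outcome. At 29 per group, the power to detect 0.51 in PPT is about 30% with SD 1.36, and about 11% with the SD of 2.62 that the same section prints. A null PPT result would be likely even if the assumed difference were real.

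**2. What each between-group result would say about shared pathways.**

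| Between-group result | Compatible explanations |
|---|---|
| Significant | One arm acts on the PAG/RVM; or both act on it to different degrees |
| Not significant | Both act equally; or neither acts; or they differ and the trial missed it |

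Each row contains both a shared and an unshared mechanism, so neither result settles the question.

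**3. Would a formal equivalence test help?** The protocol gives no margin, so the margins here are assumptions. With 29 per arm, a true difference of zero and two one-sided 5% tests, power = 2Φ(m/√(2/29) − 1.645) − 1, where m is the margin in SD units.

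- m = 0.5: 20%
- m = 0.75: 77%
- m = 1.0: 97%

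Only wide margins are workable. Even a successful test would show similar change in the two arms, not that either arm changed because of its treatment.

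**4. What the within-arm tests can show.** They test whether NRS or WOMAC changed from beginning to end. With no untreated arm, that change combines treatment effect, natural course and regression to the mean.

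Illustration for NRS, with all inputs assumed: population mean 4, SD 2, entry cut-off 3, test-retest correlation r from 0.7 to 0.5.

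- Expected score given entry: 4 + 2 × φ(0.5)/Φ(0.5) = 4 + 2 × 0.3521/0.6915 = 5.02.
- Expected fall with no treatment effect: 1.02 × (1 − r) = 0.31 at r = 0.7 and 0.51 at r = 0.5. (This 0.51 is in NRS points and has nothing to do with the PPT difference.)

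This takes the qualifying score as the baseline. Table 1 puts the eligibility screen at enrollment and NRS at the beginning and end. If these are separate readings, some or all of the regression happens before baseline and the fall is smaller, possibly near zero. Natural course would still not be separable from treatment effect.

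**The case against.** Several stronger readings are tempting, and the document does not support them.

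- *A positive primary result would contradict the hypothesis.* It would not. Sharing a pathway does not mean acting on it equally, and the Introduction nowhere claims equal effects.
- *The between-group comparison is the only analysis.* It is not. Within-group tests are planned for the ranked outcomes, and both arms are scanned before and after.
- *No result could support the hypothesis.* This is too broad. The association clause fits either between-group result.
- *The Conclusions expect relief from Tuina only.* They say Tuina would relieve pain and are silent on education. A control can be active, so the mismatch with the Introduction is in the role given to education, not a flat contradiction.
- *The interventions undercut each other.* A reader might set "The participants are to maintain their dietary habits and regular physical activity throughout the study period" against teaching "the methods used to manage the associated risks to help participants protect their knees". Keeping diet and activity stable is ordinary control of co-interventions, and the education text instructs no change in either. No conflict is shown.

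It can also be said that a shared-effect analysis may sit in an analysis plan not shown here. That is fair, and its absence from the article is not the finding. The finding is that the stated hypothesis does not match the stated sample size, VBM test and role of the control. No analysis plan can supply the untreated arm needed to show that each treatment relieves pain.

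**Conclusion.** The point holds in limited form. The first two parts of the hypothesis, that all treatments relieve pain and share pathways, are not tested by the described between-group analysis and cannot be established by the within-arm tests. The third part, the association of pain relief with the descending system, is untouched.

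The conclusion rests on the two-arm structure and the stated tests, not on any assumed figure. The regression-to-the-mean range (from near zero to about 0.5 NRS points) and the equivalence powers depend on the assumed inputs and are illustrations only. This should be corrected because it changes what the trial may claim. It does not affect the validity of the randomised comparison itself.

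**What to change.** Reconcile the Introduction, Sample Size, VBM Analysis and Conclusions around one confirmatory hypothesis, the randomised contrast: change in PAG/RVM rsFC and GMV, and change in pain, differs between patients assigned to Tuina and those assigned to health education.

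- Label the statement about all treatments and common pathways as exploratory, or remove it.
- State that pre-post change common to both arms will not be attributed to either treatment.
- Record this as a dated amendment, because enrolment began in December 2023 and the hypothesis is already published.

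No patients, scans or visits are added. The trial gives up the claim that education works or that a pathway is shared, neither of which this design can support.
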